## Abstract

**Introduction::**

Esophagectomy is a major surgery with a high degree of catabolic and post-surgical inflammatory response accompanied by high morbidity and significant mortality. Post-surgical nutritional support via enteral administration of ω-3 fatty acids has been seen to be effective although its bad tolerance. There are few clinical trials with parenteral ω-3 fatty acids in these patients. We propose to investigate the effect of combining a parenteral fish oil lipid emulsion with the standard enteral nutrition (EN) support.

**Materials and methods::**

Prospective, single-center, randomized, double-blind study in esophagectomized patients, and treated after surgery with parenteral lipid emulsions of ω-3 fatty acids or a mixture of ω-6 long-chain triglycerides/short-chain triglycerides 50%. These emulsions will be added to the standard nutritional support in continuous infusion until 5 days of treatment have been completed. Patients will be randomized 1:1:1 in Group A receiving 0.4 g/kg/d of fish-oil lipid emulsion and 0.4 g/kg/d of a lipid emulsion mixture of ω-6 long-chain fatty acids (LCT) plus medium-chain fatty acids (MCT) (total dose of 0.8 g/kg/d of lipid emulsion); Group B receiving 0.8 g/kg/d of fish oil lipid emulsion and Group C receiving 0.8 g/kg/d of LCT/MCT emulsion.

The main objective is to determine whether 5 days administration of intravenous ω-3 fatty acid lipid emulsion is effective in normalizing interleukin-6 levels compared with LCT/MCT emulsions, and whether a 0.8 g/kg/d dose is more effective than 0.4 g/kg/d. Secondary outcomes include other inflammatory markers such as C-reactive protein, tumor necrosis factor alpha and interleukin-10, and parameters of morbidity, safety, nutrition and mortality.

Samples will be collected at the time when surgery is indicated and on days 0, 1, 3, 5 and 21 to determine inflammatory, nutritional, hepatic and safety parameters. In addition, clinical follow-up will be continued throughout the hospital admision and up to 1 year after surgery.

**Discussion::**

Studies of ω-3 fatty acids administered parenterally in esophagectomized patients are scarce. This study proposes to investigate the effect of combining fish-oil lipid emulsions administered parenterally with EN support. Potential benefits include fast incorporation of lipids to the cellular membranes and to the inflammatory cascade, and the use of only 1 pharmaconutrient.

**Trial Registration::**

FAR-NP-2017-01 EudraCT number: 2016-004978-17.

https://reec.aemps.es/reec/public/detail.html searching the EudraCT number.

**Version Identifier::**

Version 2, 08/06/2017.

## Introduction

1

Esophageal cancer incidence increases with age, is more prevalent in men and is associated with risk factors such as smoking habit, obesity and alcoholism.^[1]^

This cancer is frequently associated with protein-energy malnutrition^[2]^ and usually has a poor prognosis due to late presentation and diagnosis, as well as patients not meeting criteria for curative treatment at the time of diagnosis. About 1 in 5 patients needs surgical resection.

Esophagectomy (EPG) is a major surgical intervention which involves total or partial esophageal resection and restoration of gastrointestinal continuity.^[1]^ Despite improvements in perioperative care, EPG continues to be associated with high rates of morbidity and mortality.^[1,2]^ In fact, post-operative complications are common, including both primary surgical events, such as anastomosis dehiscence or chylothorax, and adverse medical events, principally pneumonia.^[1,2]^

Nutritional support therapy is important in these patients due to the malnutrition associated with this pathology. Additionally, some enterally administered pharmaconutrients have been shown to be effective in the reduction of post-operative complications.^[2]^ Recent studies show that early enteral nutrition (EN) has other benefits: it increases immunocompetence, reduces infection rates and maintains intestinal functionality and structure. EN is cheaper and safer than parenteral nutrition, however post-operative EN is associated with tolerance problems such as: diarrhea, abdominal distension, and paralytic ileus or nausea, and only 50 percent of patients achieve their nutritional objective.^[3]^ Sometimes, symptoms become worse when caloric intake is increased, and EN discontinuation may be necessary.^[4]^

Omega-3 fatty acids, the principal components of which are eicosapenthaenoic acid and docosahexaenoic acid, are one of the pharmaconutrients with beneficial effects in post-operative morbidity. They are essential polyunsaturated fatty acids and fish oil derivates. Their administration can reduce proinflammatory cytokine production and regulate eicosanoid synthesis.^[5–7]^ Immunomodulation with ω-3 fatty acid based nutritional therapy has demonstrated benefits in reducing infectious post-operative complications and length of stay in elective gastrointestinal surgery patients, particularly in those who present with preoperative malnutrition.^[8,9]^ The enteral administration of ω-3 fatty acids in esophagectomized patients has been assessed in different studies.^[3,10–12]^ These assays verify the variability in the assimilation of ω-3 fatty acids when they are administered enterally, and show different results in relation to post-operative morbidity. However, 2 meta analyses^[13,14]^ conclude that enteral immunonutrition improves patient's morbidity without modifying their mortality.

The physiological role of ω-3 fatty acids is extensively reported, not only in maintaining nutritional homeostasis but also in the resolution of inflammatory mechanisms^[15]^ and in the course of inflammatory pathologies such as atherosclerosis or cancer. The effects of ω-3 fatty acid administration in the metabolic response are still being explored and discovered. Due to their protective effect in inflammatory processes such as colitis, ischemia-reperfusion syndrome, pain, sepsis or acute pulmonary pathology, the role of ω-3 fatty acids is relevant in artificial nutrition support.

PUFAs are precursors of proinflammatory as well as anti-inflammatory secondary messengers, and the physiological response produced depends on the balance of the lipid composition of the membrane. The eicosanoids derived from these polyunsaturated fatty acids present receptors in different kinds of cells executing different physiological functions. The study of these secondary messengers in the esophagectomized patient, may establish their correlation with the patient's clinical pathway depending on the capacity of the ω-3 fatty acids to modulate these secondary messengers.

Due to their iso-osmolarity, intravenous administration of lipid emulsions (LE) does not require a central line thereby avoiding any extra invasive treatment for the patient. In fact, LE may have protective properties for the vascular wall. Moreover, in patients considered for the study, the LE could be administered simultaneously with EN, so that gastrointestinal tract stimulation will not be interrupted, and the caloric goal achieved.

Studies of ω-3 fatty acids administered parenterally in esophagectomized patients are poorly reported in the literature. This study proposes to investigate the effect of combining fish-oil lipid emulsions administered parenterally with EN support in the framework of a randomized clinical trial. The difference between this approach and previous published studies is 2-fold:

-Parenteral administration facilitates fast incorporation of lipids to the cellular membranes, and consequently to the inflammatory cascade.^[16]^-Use of only 1 parenteral pharmaconutrient (ω-3 fatty acids) facilitates the caloric goal and enables the study of the immunomodulatory effect of 1 nutrient without interference from other nutrients. When immunonutrition is administered enterally, the commercialized products available are combinations of different immunonutrients. Lipid emulsion comprising combined long-chain ω-6 long-chain fatty acids (LCT) and medium-chain fatty acids (MCT) is proposed as a control lipid to compare the effects on immunomodulation. These emulsions have the same physical appearance as ω-3 lipid emulsion. The LCT emulsions have an active role in the immunological system but are sensitive to peroxidation, whereas MCT emulsions do not participate in the immune response and are not sensitive to peroxidation, so in consequence the combination of both has no immunomodulatory effect.^[17]^

## Methods

2

This trial is a prospective, single-center, randomized, double-blind study in patients diagnosed with esophageal cancer who post-EPG are treated with a lipid emulsion of ω-3 fatty acid or a mixture of ω-6 long-chain triglycerides/short-chain triglycerides 50%.

### Study objectives

2.1

The main objective of this study is:

To establish if the endovenous administration of ω-3 fatty-acid fish-oil lipid emulsions for 5 days in esophagectomized patients is effective in reducing inflammation – measured as seric concentration of interleukin-6 (IL-6) – compared to the administration of lipid emulsions of LCT/MCT. Additionally, to determine if doses of 0.8 g/kg/d are more effective than doses of 0.4 g/kg/d in the normalization of IL-6.

The secondary objectives aim to determine if the intravenous administration of ω-3 fatty-acid fish-oil lipid emulsions for 5 days in esophagectomized patients shows differences compared with the administration of LCT/MCT lipid emulsion with regard to:

Seric concentration of other inflammatory parameters: C-reactive protein, tumoral necrosis factor-α (TNF-α), interleukin-10 (IL-10), interleukin-8 (IL-8) and soluble interleukin-2 receptor. In addition, in the follow-up, whether these markers, alone or in combination, show equal or greater efficacy of effect on the inflammatory response compared to IL-6.Post-operative complications: suture dehiscence, chylotorax, pneumonia and other infections.Safety, measured as hepatic impairment and alterations in coagulation parameters.Nutritional parameters: albumin, prealbumin and lymphocytes.Mortality: evaluated at hospital admission and at 1 year post-surgical intervention.

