#### Study population

2.2.1

Patients diagnosed with esophageal cancer and candidates for EPG by the Ivor-Lewis or MacEwan techniques, and who meet the following **inclusion criteria**:

1.18 years old or older, any gender and any race.2.Willing and able to give their written informed consent (IC) for the study. If a subject is unable to give written IC, his legal representative may do so in his/her place.3.Having access to the digestive tract.

Patients who meet the following **exclusion criteria** will not be chosen:

1.Hypersensitivity type 1 or idiosyncratic reactions to any of the lipid emulsion components.2.Pregnant or breastfeeding women.3.Plasmatic triglycerides concentration >3 mmol/L.4.In receipt of chronic treatment with corticosteroids or immunosuppressants in the last month.5.HIV diagnosis.6.Transplanted.7.Hepatic impairment classified as Child-Pugh grade B (significative functional compromise) or grade C (decompensated disease).

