##### Subject and/or treatment withdrawal criteria

2.2.1.1

Patients can voluntarily refuse to continue in the study at any time. In addition, presentation of any adverse effect related to the treatment will lead to a treatment withdrawal and to exclusion from the study.

All patients who present with surgical complications classifiable as grade IV of the Dindo-Clavien classification^[18]^ will be excluded from the study.

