### Study variables

2.3

The main variable of this study is the variation of seric concentration levels of IL6 at randomization and on days 1, 3, 5, 21 post-surgery in esophagectomized patients receiving fish-oil lipid emulsions parenterally for 5 days compared with those receiving LCT/MCT emulsions.

The secondary variables will examine whether intravenous administration of fish-oil lipid emulsions instead of LCT/MCT for 5 days leads to differences from randomization and on days 1, 3, 5 and 21 post-randomization with respect to:

Seric concentrations of inflammatory markers: RCP, TNF-α, IL-10, IL-8 and soluble interleukin-2 receptor.Morbidity measured as post-operative complications: suture dehiscence, chylotorax, pneumonia and other infections.Safety measured as hepatic impairment (total bilirubin, alanin-aminotranspherase, aspartate-amino transpherase, gammaglutamil transpherase, alkaline phosphatase) and alteration in coagulation parameters (INR, prothrombin time, platelet count).Nutritional parameters: albumin, prealbumin and lymphocytes.Mortality measured for a year after surgical intervention.

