##### Analytical data

2.5.1.1

-Inflammatory parameters: values of IL-6, RCP, TNF-α, IL-10, IL-8 y CD25 on days 0, 1, 3, 5 and 21 post-surgery will be recorded. These values have been selected according to what is reported in the literature in similar studies.^[19–25]^ Also, these same values will be recorded pre-operatively at the time surgical intervention is indicated to show the patient's baseline inflammatory status.-Nutritional parameters: albumin, prealbumin and lymphocytes at the time surgical intervention is indicated and on days 0, 1, 3, 5 and 21.-Hepatic parameters: total bilirubin, alanin-aminotranspherase, aspartat aminotranspherase, gammaglutamil transpherase and alkaline phosphatase at the time surgical intervention is indicated and on days 0, 1, 3, 5 and 21.-Safety: INR, prothrombin time and platelet count at the time surgical intervention is indicated and on days 0, 1, 3, 5 and 21.

The total number of blood extractions per patient will be 6.

Clinical data: the following data will be recorded:

-Post-surgery complications such as chylothorax, dehiscence, pneumonia and other infections.-Mortality: from the day of surgery to 1 year following surgery.-Nutritional support: the amount of EN received by each patient will be recorded to determinate total calories administered.

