### Adverse events notification

2.7

All serious adverse events, regardless of their causal relation, will be reported to the study monitor immediately, sending a fax to [name], in a maximum of 1 working day. According to articles 43 and 44 of the RD1090/2015, which regulates clinical trials in Spain, and in accordance also with sections 25 to 27 from the regulatory document concerning implementation of normal clinical trials (6th version, May 2008), the monitor will be responsible for communicating every serious and unexpected adverse event to the competent Health Authorities. (http://www.aemps.es/actividad/invClinica/ensayosClinicos.htm).

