## Discussion

3

These days, ω-3 fatty acids are playing an increasingly emergent role in artificial nutrition, due to the discovery of their protective and immunomodulatory effects in inflammatory processes.^[20–26]^

It is known that the PUFAs of cellular membranes are precursors of secondary messengers that can act as pro-inflammatory or as anti-inflammatory agents, and physiological response depends on the balance of the lipid composition of membranes.^[12,15,16]^

The study of these secondary messengers in esophagectomized patients, may establish their correlation with the patient's clinical progress, depending on the capacity of the ω-3 fatty acids to modulate these secondary messengers.

This study combines high-risk patients with considerable inflammatory response with intravenous administration of significant quantities of ω-3 fatty-acids, and may lead to the discovery of a new pharmacological strategy that is simple, safe and cost-effective. It will also provide useful data through the study of a new mediator.

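### The safety outcome is defined by liver and coagulation tests only, so the treatment-related effects and treatment stops that the protocol recognises are not counted by arm

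*Protocol article*

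**What the plan says.** Section 2.1 (Study objectives) lists as a secondary objective "Safety, measured as hepatic impairment and alterations in coagulation parameters". Section 2.3 (Study variables) makes this operational in two parts: "Safety measured as hepatic impairment (total bilirubin, alanin-aminotranspherase, aspartate-amino transpherase, gammaglutamil transpherase, alkaline phosphatase") and "alteration in coagulation parameters (INR, prothrombin time, platelet count"). Neither section marks the list as a set of examples.

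Section 2.5.1.1 (Analytical data) schedules the same tests before surgery and on days 0, 1, 3, 5 and 21. Its clinical list covers post-surgical complications, mortality and the amount of enteral nutrition. Section 2.6.1 (Statistical analysis) compares safety parameters as a change from baseline to day 5.

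Two other sections deal with harm. Section 2.2.1.1 states that "presentation of any adverse effect related to the treatment will lead to a treatment withdrawal", and adds that the patient is then excluded from the study. Section 2.7 states that "All serious adverse events, regardless of their causal relation, will be reported to the study monitor immediately"; from there, serious and unexpected events go to the health authorities. Neither section links these events to a study variable or to a comparison between groups.

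**The concern.** The protocol treats a treatment-related adverse effect as important enough to end both treatment and participation, but its safety outcome has no place for such an event. If the text is followed as written, related effects and treatment stops do not enter the safety comparison of fish oil with LCT/MCT.

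The exclusion rule adds a second problem. A patient excluded during the 5-day infusion may contribute no later liver or coagulation values. An arm with more related effects would then be summarised on the patients who tolerated the emulsion, and its laboratory profile could look cleaner than it was. Similar laboratory values across arms could be taken as similar safety when the difference lay in events left outside the definition.

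**Working it through.** The point concerns a definition, so the main check is to set the sections side by side. No figure in the plan has to be reproduced for it.

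**1. Where each kind of harm is counted**

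| Event or measure | Recognised in | In the safety variable (2.1, 2.3)? | In another compared outcome? |
|---|---|---|---|
| Liver tests | 2.3, 2.5.1.1 | Yes | – |
| INR, prothrombin time, platelets | 2.3, 2.5.1.1 | Yes | – |
| Treatment-related adverse effect | 2.2.1.1 | No | Only if it is also a listed complication or a death |
| Treatment stop | 2.2.1.1 | No | No |
| Serious adverse event | 2.7 | No | Only if it is also a listed complication or a death |

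Section 2.6.1 offers chi-square or Fisher tests for categorical variables, but the safety variable contains no event to which they could be applied.

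**2. What exclusion could remove**

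The safety analysis looks at day 5. A patient excluded on day 2, for example, could lose the day 3, 5 and 21 samples, and so the value on which that analysis rests. If 3 of 11 patients in an arm were excluded in this way (an assumed number), the day-5 laboratory comparison in that arm would use 11 − 3 = 8 patients.

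**3. How many events to expect**

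Inputs: 33 patients (2.2.3) allocated 1:1:1 (2.2.2), so 33 / 3 = 11 per arm, and 2 × 11 = 22 in the two fish-oil arms. The 33 already includes the 10% allowance for losses. The protocol gives no rate of related effects, so a range is assumed. The chance of at least one event is 1 − (1 − p)^n.

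| Assumed rate p | n = 11 | n = 22 |
|---|---|---|
| 1% | 10.5% | 19.8% |
| 5% | 43.1% | 67.6% |
| 10% | 68.6% | 90.2% |
| 20% | 91.4% | 99.3% |

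For p = 5%, n = 22: 1 − 0.95^22 = 0.676. With few events expected, leaving out each affected patient could remove most of the clinical safety information.

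**4. What counts by arm could show**

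Take an assumed split of 3 of 11 stops in one arm and 0 of 11 in another. The exact (Clopper-Pearson) 95% interval for 3/11 is 6.0% to 61.0%. For 0/11 the upper limit is 1 − 0.025^(1/11) = 28.5%. The intervals overlap. One-sided Fisher p = C(11,3) / C(22,3) = 165 / 1540 = 0.107. The opposite split is equally likely, so two-sided p is about 0.21. Such a split deserves to be reported, but it is not evidence of a difference.

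**The case against.** The strongest reply is that this is an omission in a condensed article. Naming laboratory safety markers does not say that adverse events go unreported, and a table of adverse events by arm is routine content of a full protocol, case report form or analysis plan. This stands against any claim that these events can never be counted: the article cannot show that. It does not remove the point, because objectives and variables are protocol content. Here they are stated twice, as a definition that the article's own withdrawal and reporting rules do not fit.

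A second reply is that clinical harm is compared elsewhere. Complications and one-year mortality are separate secondary outcomes, and section 2.5.1.1 gives its complications as examples, so other complications may be recorded. That is correct and limits the gap. A related effect that is neither a complication nor a death, and a treatment stop as such, still have no outcome.

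Several stronger readings are tempting but are not supported:
- **Bleeding and infusion reactions as recognised risks.** The article names neither. Coagulation is something it measures, and "Hypersensitivity type 1 or idiosyncratic reactions to any of the lipid emulsion components" appears only as a reason not to enter a patient.
- **The comparison of 0.8 with 0.4 g/kg/d resting on safety laboratory values.** Section 2.1 sets that comparison for IL-6. The safety objective compares fish oil with LCT/MCT.
- **A stated aim of proving safety.** The phrase "a new pharmacological strategy that is simple, safe and cost-effective" is in the Discussion, as something to which the study may lead. It is not an objective.

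**Conclusion.** The point holds in a limited form. The safety outcome is fixed too narrowly for the protocol's own rules: as written, it counts no treatment-related effect, treatment stop or serious adverse event by arm, and the exclusion rule may also remove later laboratory values from the affected patients. The change should be made, but the gap does not threaten the primary IL-6 comparison.

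The size cannot be fixed from the document. It depends on the rate of related effects, taken above as 1% to 20%, and on whether exclusion ends data collection and analysis for the patient, which the article does not spell out. With about 11 patients per arm, counts by arm describe what happened; they will not establish or rule out a difference. A full protocol or analysis plan that already tabulates these events by arm would reduce the point to bringing sections 2.1 and 2.3 into line with it.

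**What to change.** Extend the safety variable in sections 2.1 and 2.3 to include the number of patients in each randomized arm with:
- any serious adverse event;
- any treatment-related adverse effect;
- any treatment stop, with its reason.

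Report these with exact 95% intervals beside the laboratory values, as description.

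Reconcile sections 2.1 and 2.3 with 2.2.1.1 and 2.7. The text should say that patients who are withdrawn or excluded are still counted in these safety results under their randomized arm, and whether their later laboratory values are collected and used. This concerns counting and reporting only; the clinical rule for stopping treatment is not at issue here.

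The cost is an amended variable list, a short adverse-event page in the Data Collection Logbook and one table. Sections 2.2.1.1 and 2.7 already require most of these events to be identified, so the extra recording is mainly for non-serious related effects and reasons for stopping. Sample size and the primary analysis are unchanged.
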